**Introduction**

Temporomandibular dysfunction (TMD) describes clinical conditions involving the temporomandibular joint (TMJ), muscles of mastication, as well as associated tissues.^1^

The prevalence of TMD has been reported of 8% to 15% with females affected more than males^2^ with the peak prevalence around 35 to 45 years.^3^

TMD has been considered a major health concern and a main cause of chronic orofacial pain having negative impact on daily living activities and life quality, Whereas more than a quarter of the general population are subject to TMD at some point in their lives.^4^

Manifestations of TMD include pain around the TMJ, limitations in jaw motion, and TMJ sounds such as clicking or crepitus with movement.^1^

Physiotherapy (PT) is currently considered as a managing strategy for TMD disorders aiming to restore normal mandibular function through pain relief, decreasing inflammation and promoting tissue healing.

PT interventions, include manual therapy, exercises, and ultrasound as well as laser therapy. ^5–7^

One of the recommended PT methods for pain relief, decreasing inflammation and promoting tissue healing is Low level laser therapy [LLLT].^8–10^ however, only few studies discussed its use in the management of TMD. ^11–16^

**Statement of the problem**

There is still limited evidence to support clinical effectiveness in TMD treatment due to the lack of agreement in defining TMD, inclusion and exclusion criteria and use of valid and reliable outcome measures.^17^

Also, despite improving, still many practicing dentists, physicians, and physical therapists (PTs) are not formally trained in the diagnosis and treatment of TMD.^18,19^

There is a need to objectively guide both assessment and treatment procedures.

One of the currently used methods is Surface electromyography (sEMG) that has been proposed as a noninvasive tool in TMD objective assessment providing muscular activity at rest and during functional activities. ^18,20,21^

Unfortunately, the effect of LLLT application on sEMG activity of masticatory muscles has been poorly investigated.^21,22^

**Purpose of the study**

To assess the efficacy of low-level laser therapy (LLLT) as compared to occlusive splint therapy (OST) on the TMJ opening index (TOI) and sEMG of masticatory muscles.

**Materials and methods**

**Design**

A double-blinded parallel group randomized controlled trial. An external assessor with more than 10 years clinical experience, blinded to both treatment and results was recruited to deliver the LLLT.

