**Outcome measures:**

**Primary outcome:**

The temporomandibular opening index (TOI) is calculated by the formula ^23^ :

TOI= Passive opening _mm_ -Maximum voluntary opening _mm_ X 100

Passive opening _mm_ + Maximum voluntary opening _mm_

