**Secondary outcomes:**

1. Surface EMG (sEMG):

For recording, a surface electromyograph (Myotronics-Noromed, Inc., Tukwila WA, USA), with 8-channels, simultaneous acquisition, common grounding to all channels, and filters of 50 Hz electromyography with disposable electrodes was used.

Subjects will be seated on chairs with back and head rests to allow assessment from a relaxed position.

The right masseter (RM), left masseter (LM), right anterior temporal (RAT), left anterior temporal (LAT), right sternocleidomastoid (RSM), and left sternocleidomastoid (LSM) muscles will be recorded.

Electrode positions are adopted from Castroflorio et al., 2005 for the left and right masseter muscles (LM, RM) and the left and right anterior temporal muscles (LAT, RAT) ^20^ as well as Falla et al., 2002 for the left and right sternocleidomastoid muscle (LSM, RSM). ^24^

The ground electrode will be positioned on the forehead as a common reference to the amplifier’s differential input.

1. Visual analogue scale

Pain intensity will be assessed by the Visual Analogue Scale (VAS) where no pain is rated as 0 mm and worst possible pain as 100 mm.^25,26^

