**Procedures**:

Laser group: A low-level gallium arsenide diode (Biolase, USA) at a 940 nm wavelength with 0.2 W output power and 2 J energy will be used. The device will be calibrated, and the probe to be disinfected prior to every treatment.

The Masseter and Temporalis muscles will be bilaterally assessed with constant pressure to define tenderness.

LLLT will be applied perpendicular to each tender point of the intended muscles for 10 seconds with an energy density of 2.5 J/cm^2^.

Sessions will be scheduled 3 days a week (every other day) over a period of 4 months.

1. Occlusive splint:

A soft occlusal splint (vacuum-formed) made from a 2-mm-thick elastic rubber sheets was used. ^27^

Splints will be individually designed for the upper arch of each patient. An alginate imprint of the maxillary arch was taken to fabricate a master cast of the maxilla.

Participants will be instructed to wear the splint at all times except during mealtimes and oral hygiene.

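### The double-blind label is unsupported: the only person called blinded delivers the laser, no masking of patients is described, and no blinded measurer of TOI or sEMG is named

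*Protocol*

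**What the plan says.** The Design section describes the trial as follows: "A double-blinded parallel group randomized controlled trial". It names one blinded person and gives that person one task: "An external assessor with more than 10 years clinical experience, blinded to both treatment and results was recruited to deliver the LLLT".

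Procedures describes two treatments that look and feel different. In the laser arm, "LLLT will be applied perpendicular to each tender point of the intended muscles for 10 seconds", and "Sessions will be scheduled 3 days a week (every other day) over a period of 4 months". In the splint arm, "Participants will be instructed to wear the splint at all times except during mealtimes and oral hygiene". No sham laser, placebo splint or double dummy is mentioned.

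Under Outcome measures, the primary outcome is the TOI, computed from passive opening and maximum voluntary opening. The secondary outcomes are sEMG and pain on a 0 to 100 mm VAS. The section does not say who takes the TOI and sEMG readings, or whether that person is kept from allocation.

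**The concern.** Double-blinded is a claim about the design, and readers rely on it when they judge how far a treatment difference could be an artefact of measurement. Here the only sentence that supports the claim assigns blindness to someone who cannot have it. Nothing else in the protocol says who is masked or how.

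The primary outcome is at stake. TOI is built from two opening measurements taken at an examination. If the measurer knows the arm, and this affects how either opening is obtained or read, the laser-splint comparison is biased. A larger sample does not remove such a bias, and readings already taken unblinded cannot be repaired. Who is blinded is a design matter that belongs in the protocol. It is not a detail usually left to a statistical analysis plan.

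**Working it through.** The protocol states no figure to reproduce on this point. The check is mainly a comparison of its sections, followed by a short calculation on the TOI formula.

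**Step 1: who is said to be blinded.** Design names one person, the external assessor, as blind to treatment and to results. The only task given to that person is delivering the LLLT. Procedures says the laser is applied to each tender point for 10 seconds. Whoever does this knows the treatment, so being blind to treatment and delivering the laser cannot both be true.

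**Step 2: whether patients are masked.** The comparison is laser against splint. A laser patient attends sessions 3 days a week over 4 months. A splint patient has an individually made upper-arch device, worn except at meals and during oral hygiene. The exclusion criteria rule out prior laser therapy, which could help to mask a sham laser, but no sham is described. Under the procedures as written, a patient can tell which treatment she receives.

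**Step 3: whether a blinded measurer is described.** Outcome measures names none. If the external assessor also measures, the measurer knows who received laser. If someone else measures, nothing says that this person is blind. Neither case supports the label.

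**Step 4: how sensitive the primary outcome is.** With P for passive opening and M for maximum voluntary opening, both in mm, the protocol's formula is

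TOI = 100 × (P − M) / (P + M).

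The protocol gives no openings, so the values below are assumptions chosen to span a range. Each row adds 1 mm to P and holds M fixed.

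| M (mm) | P (mm) | TOI before | TOI after | Change in points | Relative change |
|---|---|---|---|---|---|
| 30 | 35 to 36 | 100 × 5/65 = 7.69 | 100 × 6/66 = 9.09 | 1.40 | 18% |
| 40 | 43 to 44 | 100 × 3/83 = 3.61 | 100 × 4/84 = 4.76 | 1.15 | 32% |
| 45 | 47 to 48 | 100 × 2/92 = 2.17 | 100 × 3/93 = 3.23 | 1.05 | 48% |

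TOI is a small difference divided by a large sum, so 1 mm moves it by about 1.1 to 1.4 points. The relative change grows as the gap between P and M narrows.

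**The case against.** The best defence is that the sentence in Design is a drafting slip. The word assessor, and the mention of being blind to results, suggest that the blinded person was meant to measure. The protocol never says that this person takes no measurements. This is plausible, and it means a reader should not infer that a blinded measurer was deliberately moved to treatment. It does not remove the defect: the text as written contradicts itself and leaves the measurer undefined.

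Other stronger inferences are tempting, and the protocol does not support them:

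- **Blinding is impossible here.** It is impossible for the person delivering the laser, as the sentence stands. For patients, the protocol shows only that no masking is described. A sham or double-dummy design is conceivable. The 3 x 2 layout under Statistical analysis does not say which factor has three levels, but no masking is described for any group.
- **VAS is open to examiner bias.** VAS is the patient's own rating. Its exposure comes through patients who know their treatment.
- **Splint patients will reveal their arm by arriving with the device in place.** The wearing instruction makes this a reasonable worry, but assessment visits are not described.
- **Passive opening depends on the force the examiner applies.** This is plausible, but the protocol gives only the formula and not how passive opening is obtained.
- **The 1 mm calculation measures the bias.** It does not. Nothing shows that an unblinded measurer would create a 1 mm difference between arms, and the protocol gives no standard deviation or target difference for comparison. The percentages look large partly because TOI starts small.

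It is also fair to object that simply swapping roles may not be enough. The protocol names no other clinician who could deliver the laser, and a swap cannot restore blindness for patients the assessor has already treated. Nor does a blinded measurer remove the influence of patients who know their arm on maximum voluntary opening, which is by name a voluntary effort. These points stand and shape the fix.

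**Conclusion.** The point holds. The blinding statement is wrong as written, because the person delivering the laser cannot be blind to it. The double-blind label has no support elsewhere in the protocol, since no masking of patients is described and no blinded measurer of TOI or sEMG is named. The primary outcome therefore has no described protection from measurement bias.

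These conclusions rest on the text alone. The size is known only as a sensitivity, over the three assumed pairs of openings. The direction and amount of any actual bias cannot be derived from the protocol. The matter should be settled before further measurements are taken.

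**What to change.** 1. **Correct the sentence in Design** so that the person delivering LLLT is not called blinded.
2. **Name the measurer.** TOI and sEMG should be taken by the external assessor, or by another person already on the study, who does not treat the patients being measured and is kept from allocation. If the external assessor takes this role, the protocol must say who delivers the laser instead. Patients whom the assessor has already treated need a different measurer.
3. **Protect the measurement.** State that splints are out before the measurer sees the patient, and that patients are asked not to disclose their arm.
4. **Correct the label** to assessor-blinded, with patients and treating clinician unblinded. For any patients measured by someone who knew their arm, use open-label.
5. **State the remaining limitations.** VAS and the voluntary-opening component of TOI come from patients who know their treatment, and a blinded measurer does not change that.

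The cost is protocol wording, some reallocation of tasks and a less favourable blinding label. The sample size and the outcome definitions do not change.

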**Subjects**

This study will be conducted in accordance with the Declaration of Helsinki after approval is obtained from the research ethics committee, Faculty of Physical Therapy, Cairo University, Egypt. The protocol will be registered in the ClinicalTrials.gov.

Sample size was calculated through estimates for the means and standard deviations that will be obtained from a pilot study on 15 patients to receive the treatment protocol.

**Inclusion will be limited to**:

Females less than 30 years of age, diagnosed with unilateral myogenous TMD, having complete permanent dentition and showing normal occlusion.

Subjects were excluded if they met one or more of the following criteria:

Prior experience of Laser therapy, systemic diseases (rheumatoid arthritis, ankylosing spondylitis, diabetes… etc.; history of trauma in the TMJ or cervical regions; neurological disorders, muscular diseases; cervical pain; bruxism, pregnancy; currently on medication (analgesic, anti-inflammatory, muscle relaxants or anti-depressants) current use of dental prosthetics; previous orthodontal treatments; or fixed restorations affecting occlusal surfaces.

**Outcome measures:**

**Primary outcome:**

The temporomandibular opening index (TOI) is calculated by the formula ^23^ :

TOI= Passive opening _mm_ -Maximum voluntary opening _mm_ X 100

Passive opening _mm_ + Maximum voluntary opening _mm_

**Secondary outcomes:**

1. Surface EMG (sEMG):

For recording, a surface electromyograph (Myotronics-Noromed, Inc., Tukwila WA, USA), with 8-channels, simultaneous acquisition, common grounding to all channels, and filters of 50 Hz electromyography with disposable electrodes was used.

Subjects will be seated on chairs with back and head rests to allow assessment from a relaxed position.

The right masseter (RM), left masseter (LM), right anterior temporal (RAT), left anterior temporal (LAT), right sternocleidomastoid (RSM), and left sternocleidomastoid (LSM) muscles will be recorded.

Electrode positions are adopted from Castroflorio et al., 2005 for the left and right masseter muscles (LM, RM) and the left and right anterior temporal muscles (LAT, RAT) ^20^ as well as Falla et al., 2002 for the left and right sternocleidomastoid muscle (LSM, RSM). ^24^

The ground electrode will be positioned on the forehead as a common reference to the amplifier’s differential input.

1. Visual analogue scale

Pain intensity will be assessed by the Visual Analogue Scale (VAS) where no pain is rated as 0 mm and worst possible pain as 100 mm.^25,26^

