**Statistical analysis:**

The SPSS Package version 25 for Windows (SPSS, Inc., Armonk, NY: IBM Corp) will be considered for the analysis.

Data will be tested for homogeneity and a 3 x 2 MANOVA mixed design was used for comparing variables in different groups and measurement times.

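### Patients have one-sided disease, but the sEMG outcome is labelled only right and left; analysed as labelled, it pools affected with unaffected muscles

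*Protocol*

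**What the plan says.** - **Population** (Protocol, inclusion criteria): entry is limited to patients "diagnosed with unilateral myogenous TMD". No criterion fixes which side must be affected.
- **sEMG outcome** (Protocol, Secondary outcomes): the muscles are "The right masseter (RM), left masseter (LM), right anterior temporal (RAT), left anterior temporal (LAT"), followed by "right sternocleidomastoid (RSM), and left sternocleidomastoid (LSM) muscles will be recorded". There are six channels, each named by right or left. No affected-side label or asymmetry index appears.
- **Laser treatment** (Protocol, Procedures): "The Masseter and Temporalis muscles will be bilaterally assessed with constant pressure to define tenderness". Then "LLLT will be applied perpendicular to each tender point of the intended muscles for 10 seconds". Treatment therefore follows tenderness, on whichever side it is found.
- **Splint** (Protocol, Procedures): made for the whole upper arch, so not one-sided.
- **Analysis** (Protocol, Statistical analysis): "a 3 x 2 MANOVA mixed design was used for comparing variables in different groups and measurement times". The two factors named are group and time.
- **Sample size** (Protocol, Subjects): "Sample size was calculated through estimates for the means and standard deviations that will be obtained from a pilot study on 15 patients". No number of patients, power, effect size or standard deviation is given.

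**The concern.** The label of the outcome does not match the structure of the disease. In a trial of one-sided TMD, the right masseter is the affected muscle in some patients and the unaffected muscle in the rest. If the sEMG variables go into the analysis as labelled, every one of them is such a mixture.

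Two things follow. First, if affected and unaffected muscles differ in activity or in response, the mixture has more spread than either component. Second, if treatment changes the affected side more than the other, the mean arm difference in each right or left variable is smaller than the difference on the affected side.

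sEMG is a secondary outcome, but it is named in the Purpose of the study, and the poorly investigated effect of laser on sEMG is part of the stated rationale. A weak or null sEMG result produced by the labelling could be misread as absence of effect.

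**Working it through.** **No stated figure to reproduce.** The protocol gives no sample size, effect size, standard deviation or power. What follows is an illustration on assumed inputs.

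**Assumed inputs**
- d = 0.8: standardised between-arm effect on the affected side, within-side SD = 1.
- p = 0.5: share of patients affected on the right.
- r: effect on the unaffected side as a fraction of d, varied from 0 to 1.
- 26 patients per arm, two-sided alpha 0.05, two-sample t-test. With affected-side coding this gives 81% power.

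**Step 1, mean effect.** Effect on a right-side variable = p·d + (1 − p)·r·d. With p = 0.5 this is d·(1 + r)/2. At r = 0 it is 0.8 × 0.5 = 0.40; at r = 0.5 it is 0.8 × 0.75 = 0.60; at r = 1 it is 0.80.

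**Step 2, added variance.** In the arm showing the effect, mixing adds p(1 − p)·[d(1 − r)]². At r = 0 this is 0.25 × 0.64 = 0.16. Averaged over two arms, the variance is (1.16 + 1)/2 = 1.08, so the effective d is 0.40/√1.08 = 0.385.

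**Step 3, power and sample size**

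| r | share of effect kept | effective d | power at 26 per arm | n per arm for 80% |
|---|---|---|---|---|
| 0 | 50% | 0.385 | 28% | 107 |
| 0.25 | 62.5% | 0.489 | 41% | 67 |
| 0.5 | 75% | 0.594 | 56% | 46 |
| 0.75 | 87.5% | 0.698 | 69% | 34 |
| 1 | 100% | 0.800 | 81% | 26 |

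**Step 4, uneven split.** With p = 0.7 and r = 0, the right-side variable keeps 70% of the effect and the left-side variable 30%.

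**Step 5, noise from a level difference.** If affected and unaffected muscles differ by g SD in level, an even mixture has variance 1 + 0.25g² in both arms: SD 1.03 at g = 0.5 and 1.12 at g = 1. This applies to raw levels. Analysing change over time removes the part of the gap that is stable.

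**Step 6, does entering both sides in a MANOVA restore the loss?** Take p = 0.5, r = 0 and correlation ρ between sides, ignoring the added variance in Step 2. The squared multivariate distance is 0.5d²/(1 + ρ) for the right/left pair and d²/(1 − ρ²) for the affected/unaffected pair. The ratio is 0.5(1 − ρ): 50% at ρ = 0 and 20% at ρ = 0.6. So the loss is not restored when r = 0.

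**Step 7, chance imbalance.** With 26 per arm and p = 0.5, the arms differ by 5 or more right-sided patients about 21% of the time.

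**The case against.** The strongest reply is that the sEMG paragraph is partly a recording list. It sits among equipment, seating and electrode positions, says the muscles will be recorded, and does not state that the right and left channels are the units of analysis. Recording both sides is also exactly what affected-side coding needs, and a statistical analysis plan that is not shown could do the recoding. This stands in part: the protocol does not expressly commit to a right/left analysis. But right/left is the only identification of the outcome it gives, and nothing links a channel to the affected side.

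Second, a reader might infer that the treatment effect is certainly diluted, with a treated diseased muscle averaged against an untreated healthy one. The documents do not support that. The splint spans the whole arch, tenderness is sought on both sides, and laser goes to any tender point. If both sides respond equally, there is no dilution.

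Third, a reader might take the fall from 81% to 28% as the trial's loss of power. It is the worst case in a range built wholly on assumed values, in a univariate test rather than the planned MANOVA.

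Fourth, a reader might infer that a chance imbalance in affected side biases the comparison. It does not. Under randomisation it is random error that the standard error reflects, and the comparison over time reduces it further.

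Finally, nothing in the documents requires the sternocleidomastoid or unaffected-side channels to be relegated to exploratory status.

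**Conclusion.** The point holds in conditional form. Two facts come from the text: one-sided disease at entry, and sEMG channels identified only by right and left with no side factor named in the analysis. Unless every patient is affected on the same side, which no criterion requires, analysis under those labels pools affected and unaffected muscles.

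The size of the loss cannot be derived from the documents. With an even split it is governed by r alone as a share of effect, (1 + r)/2, which runs from half the effect lost to none. The power figures of 28%, 56% and 81% also need the assumed d = 0.8 and 26 per arm.

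The consequence is confined to a secondary outcome. Neither the opening index nor the pain scale is defined by side. It is still worth acting on, because affected-side coding is the better-fitting definition for a measure named in the study's purpose, and it loses essentially nothing if the two sides respond alike.

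**What to change.** 1. Record the affected side for every patient at baseline.
2. In the sEMG outcome section, keep the six recorded channels but define the analysis variables as affected-side and unaffected-side masseter, anterior temporal and sternocleidomastoid, in place of right and left.
3. State that baseline is taken into account for each variable, and word the Statistical analysis section so that it refers to these variables.

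Cost: one baseline data item already known from the unilateral diagnosis, a few lines of protocol text, and recoding of channels already recorded. No extra visits, measurements or patients are needed.

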**Procedures**:

Laser group: A low-level gallium arsenide diode (Biolase, USA) at a 940 nm wavelength with 0.2 W output power and 2 J energy will be used. The device will be calibrated, and the probe to be disinfected prior to every treatment.

The Masseter and Temporalis muscles will be bilaterally assessed with constant pressure to define tenderness.

LLLT will be applied perpendicular to each tender point of the intended muscles for 10 seconds with an energy density of 2.5 J/cm^2^.

Sessions will be scheduled 3 days a week (every other day) over a period of 4 months.

1. Occlusive splint:

A soft occlusal splint (vacuum-formed) made from a 2-mm-thick elastic rubber sheets was used. ^27^

Splints will be individually designed for the upper arch of each patient. An alginate imprint of the maxillary arch was taken to fabricate a master cast of the maxilla.

Participants will be instructed to wear the splint at all times except during mealtimes and oral hygiene.

